### Subject participation and data collection

A study team member will attend each participating antenatal clinic for subject recruitment. All women attending the antenatal clinic will be briefly informed of the study and entry criteria in a group setting. Women willing to be measured and potentially participate will be offered measurement of MUAC and screened for study eligibility.

All women meeting eligibility criteria will be offered enrollment and agree via informed consent. Informed consent will be obtained by the on-site study coordinator. All participants who are 16 years of age or older will be able to consent for themselves as adults. If a participant who is younger than 16 wants to participate in the study, they will be required to have consent from a parent or guardian. Upon enrollment, the participant will be interviewed. Demographic information will be recorded, as well as, time of last menses, estimated date of delivery, and fundal height. Anthropometry will include current weight, height, MUAC, and weight history if available. Available medical records of the women will be reviewed with attention to any current or previous pregnancy complications and medications. Subjects will answer a standard clinical symptoms questionnaire, a food frequency questionnaire, and a Household Food Insecurity Access Scale (HFIAS).

Participants will return for follow-up every 2 weeks for measurements and provision of food until delivery. Since birth measurements are primary outcomes, a birth weight team will be identified and trained in order to obtain accurate birth measurements within 48 h of delivery.

Participation in the study will continue throughout pregnancy, and follow-up with the mother and infant will continue until 6 months postpartum. Mothers and infants will be followed at usual infant clinic follow-up at 6 weeks, 3 months, and 6 months post-partum contact point clinic. Infant weight, linear growth, and morbidity will be monitored. Maternal weight, MUAC and morbidity will be assessed at these visits, as well.

### Data monitoring

The primary investigator will be responsible for the overall management of the trial. The on-site investigator will be responsible for day to day management of clinic sites. Adverse events have been defined as any reactions to RUSF, emesis, diarrhea, or rashes suggestive of food allergy.

To monitor the safety of participants, a data safety monitoring meeting will be held every other month. The meeting will be convened by the Director of Nutrition for the Ministry of Health and Sanitation for the government of Sierra Leone. Present at this meeting will be the director, a study nurse, the district health officer, and one of the investigators. At the meeting routine morbidity data, enrollment data, and participant satisfaction will be reviewed. Minutes of these meetings will be recorded and forwarded to the Sierra Leone Ethics and Scientific Review Committee (SLESRC).

A special inquiry will be convened whenever a serious adverse event is discovered. At any time a study staff member is informed about an unexpected event of a participant by a health surveillance assistant, national clinic staff, or community member, this will be reported to the Director of Nutrition for the Ministry of Health and Sanitation for the government of Sierra Leone within 24 h. Information will be gathered, and a summary of the event will be given to the data safety monitoring board within 24 h of being informed. The event will be reviewed in detail by the principle investigator and if the information supports the concern that this could be study related, an independent physician will be asked to review the case and render an opinion. The findings and conclusions will be recorded and forward to SLESRC and the Washington University IRB.

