### Outcome measures

The primary outcome measure of interest will be birth length in centimeters. The secondary outcome measures of interests include the total and average weekly maternal weight gain, recovery from maternal malnutrition identified as a MUAC > 23, newborn head circumference, birth weight, infant linear and ponderal growth, and infant survival at 3 months and 6 months.

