### Interventions to reduce inflammation

The intervention group will receive a package of five interventions aimed at decreasing the burden of infections in pregnant women in order to decrease the risk of stillbirth, fetal growth restriction, and premature delivery. This package will include an insecticide-treated mosquito net at the time of enrollment, sufadoxine-pyrimethamine given every 4 weeks beginning at 13 weeks gestation, azithromycin given at the time of enrollment and at 28–34 weeks of gestation, single dose of albendazole at enrollment, and testing and treatment for bacterial vaginosis at enrollment and again in the third trimester. Table 4 details the anti-inflammatory interventions.

**Table 4 Tab4:** Anti-Inflammatory Interventions, Dosing, and Timing of Administration

Intervention	Dose	Time of administration
Insecticide-treated mosquito net	n/a	• Enrollment
Sulfadoxine-pyrimethamine	1500 mg/ 75 mg	• Enrollment or 13 weeks gestation, whichever is later • Every 4 weeks until delivery
Azithromycin	1 g	• Enrollment or second trimester, whichever is later • Weeks 28–34
Albendazole	400 mg once	• Enrollment or second trimester, whichever is later
Testing and treatment for bacterial vaginosis with metronidazole	750 mg PO daily for 7 days	• Enrollment • Weeks 28–34

The control group will receive the current recommendations of the government of Sierra Leone, which includes 60 mg iron and 400 μg folic acid supplementation starting at enrollment, an insecticide-treated mosquito net at the time of enrollment, three doses of sulfadoxine-pyrimethamine during second and third trimester, and a single dose of albendazole for deworming at enrollment.

Table 5 provides a summary of the schedule of activities and interventions for subjects by week of study participation.

**Table 5 Tab5:** Schedule of activities/ interventions for subjects by week of study participation

	Study Period									
	Enrollment									
Week	0	2	4	6	8	Third trimester	Delivery	6 weeks post-partum	3 months post-partum	6 months post-partum
Enrollment:										
Eligibility Screen	X									
Informed consent	X									
Socio-demographic questions	X									
Assessments:	X				X					
HFIAS^a^, Food frequency questionnaire	X				X					
Clinic visit for intervention and control food supply	X	X	X	X	X					
Adherence/educational messages	X	X	X	X	X					
Surveillance of clinical events	X	X	X	X	X					
Maternal anthropometric measurements	X	X	X	X	X					

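### The only stated adverse-event definition is built on the food, so adverse-event counts are not like-for-like between arms, and no listed outcome shows the effect on stillbirth

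*Protocol article*

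**What the plan says.** The protocol article gives one definition, under Data monitoring: "Adverse events have been defined as any reactions to RUSF, emesis, diarrhea, or rashes suggestive of food allergy".

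The section Interventions to reduce inflammation shows that food is only part of the difference between arms. Intervention women have "azithromycin given at the time of enrollment and at 28–34 weeks of gestation", "Testing and treatment for bacterial vaginosis with metronidazole", and sulfadoxine-pyrimethamine "Every 4 weeks until delivery". Control women have "three doses of sulfadoxine-pyrimethamine during second and third trimester". Both arms get albendazole and a bed net. The same section says the package is given "in order to decrease the risk of stillbirth, fetal growth restriction, and premature delivery".

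Under Outcome measures, the only survival item is "infant survival at 3 months and 6 months". Stillbirth and miscarriage are not on that list, nor among the analyses named under Statistical analysis.

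The article describes other safety capture:
- Data monitoring provides a special inquiry for each serious adverse event and 24-hour reporting of unexpected events that staff hear about. On the safety meeting held every other month it says: "At the meeting routine morbidity data, enrollment data, and participant satisfaction will be reviewed".
- Data management and analysis has morbidity and mortality recorded on standard forms.
- Table 5 lists clinical-event surveillance at study visits.

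**The concern.** The trial tests a bundle of a food and several drugs, but the definition fits a trial of the food alone. It has three weaknesses.

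- One of its terms can apply in one arm only.
- Another depends on attribution to food, made by field staff who know the allocation.
- It names no reaction to any drug and no pregnancy loss, although drug exposure differs by arm and stillbirth is a stated target.

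The Discussion offers the bundle as a possible model for national programmes. A reader of the results will want to know whether it caused more harm than standard care and whether it changed the number of losses. A table of adverse events built on this definition would not answer the first question fairly, and no listed outcome addresses stillbirth.

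**Working it through.** The point rests on wording, and no stated figure bears on it. The check sets each kind of event against the definition and against the other routes.

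| Event | Intervention arm | Control arm | Other route stated |
|---|---|---|---|
| Reaction to the study food | Counts, because RUSF is named | Supercereal is not named; counts only as emesis, diarrhoea or food-type rash | Morbidity forms |
| Emesis, diarrhoea | Counts, any cause | Counts, any cause | Morbidity forms |
| Rash judged food-allergic | Counts, on unblinded judgement | Same rule | Morbidity forms |
| Rash judged drug-related | Outside the definition | Outside the definition | Morbidity forms, unexpected-event report |
| Other drug reaction | Outside, unless emesis or diarrhoea | Same rule | Same |
| Miscarriage, stillbirth | Not named | Not named | None names it; possibly a serious or unexpected event |
| Maternal or infant death | Not named | Not named | Mortality data; infant survival at 3 and 6 months |

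**Which way the counts lean.** Naming RUSF adds events in the intervention arm only. Leaving out drug reactions removes more events from the arm with more drug exposure. These pull in opposite directions, so the net direction is unknown.

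**Difference in exposure.** Azithromycin (two doses) and metronidazole (after testing) appear only in the intervention arm's list. For sulfadoxine-pyrimethamine, assume delivery at 40 weeks. A start at week 13 gives doses at weeks 13, 17, 21, 25, 29, 33 and 37. That is 7 doses against 3 in control, a difference of 4. A start at week 28 gives weeks 28, 32 and 36, which is 3 doses and no surplus. The contrast therefore runs from 0 to 4 doses according to when a woman enrols.

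**Scope.** 1514 / 2 = 757 women per arm, so one term of the definition can apply to 757 of 1514.

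**What a loss outcome could show.** The documents give no loss rate, so control rates of 1%, 3% and 5% are assumed. With two-sided 5% significance and 80% power, the number needed per arm is n = (1.960 + 0.842)² × [p0(1 − p0) + p1(1 − p1)] / (p1 − p0)². For 3% against 6% this gives 7.85 × (0.0291 + 0.0564) / 0.03² = 746, within 757. Moving p1 in steps of 0.05 percentage points gives the smallest detectable rate in the other arm:

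| Assumed rate in one arm | Detectable, 757 per arm | Detectable, 600 per arm |
|---|---|---|
| 1% | 3.05% | 3.40% |
| 3% | 6.00% | 6.45% |
| 5% | 8.65% | 9.15% |

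Only large differences would reach significance. Loss counts by arm are worth having as estimates with intervals, not as a powered test.

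**The case against.** The strongest reply is that harms are captured well beyond one sentence. Emesis and diarrhoea are listed without a cause, so they count in both arms and can reflect a drug. Morbidity and mortality are recorded for everyone, clinical events are under surveillance at study visits, serious events trigger an inquiry, unexpected events are reported within 24 hours, and infant survival is compared between arms. Controls also receive sulfadoxine-pyrimethamine and albendazole, and metronidazole follows testing, so the drug contrast is narrower than the full list suggests. A fuller definition of serious events, and the event forms, may stand in the full protocol.

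Most of this stands. A reader might infer that drug harms and losses go uncounted, or that the arms cannot be compared for safety at all. The documents do not support that. Nor do they support the inference that the safety meeting reviews a lopsided event list, because what it reviews is routine morbidity. A reader might also infer that survival differences distort mean birth length. The documents give no loss rate from which to size this, and the handling of losses in that analysis commonly belongs to the analysis plan, which is not shown.

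The reply does not repair the definition itself. The article commits to those words. The term serious adverse event is not defined, and the unexpected-event route starts only when someone tells the staff. Events on these routes are reviewed case by case for relatedness to the study, with no stated tabulation by arm. None of the routes names fetal loss.

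**Conclusion.** The concern holds in a limited form. Followed as written, the definition gives adverse-event counts that are not like-for-like: it is partly specific to one arm, relies on unblinded attribution to food, and names neither drug reactions nor pregnancy losses. Separately, stillbirth is an aim of the package that no listed outcome measures.

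The size cannot be stated as a number, and even the direction of the net distortion in the counts is open. The conclusion assumes that the article's definition is the one in force. If the full protocol has a wider one, the article misstates it and still needs correcting. The point concerns safety reporting and the outcome list. It does not undermine the primary comparison of birth length, and it should be put right without being treated as fatal.

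**What to change.** Replace the definition with one used identically in both arms, whatever the suspected cause: any new symptom, any rash, any suspected reaction to any study food or drug, hospital care, and death of mother or infant. Record these at the existing fortnightly visits and at delivery. State what makes an event serious, and say that counts will be tabulated by randomised arm.

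Add miscarriage/stillbirth as a secondary outcome, tabulated by randomised arm with all randomised women as denominator and the number with unknown pregnancy outcome shown. Tabulate maternal and early neonatal deaths by arm as well. Preterm birth is optional: Eligibility criteria uses fundal height as the measure of gestational age, so its dating would be rough.

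The cost is a change of wording and forms and somewhat more event recording. The visits, the birth measurement team and the standard forms already exist. Trial status says recruitment is under way, so the amendment should say how events in women already enrolled will be recovered.

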### Randomization and blinding

Subjects will be randomized to receive the RUSF or the standard of care (supercereal, oil, and iron and folic acid tablets), using a random number generator which prospectively assigns participants to a study group. Since RUSF is visually distinct from flour, neither the study subjects nor the research study team members working directly with participants will be blinded. Study managers will be blinded to treatment during data analysis.

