### Data management and analysis

Clinical data including demographics, anthropometry, morbidity, and mortality data will be collected by field workers using standardized forms. Field workers will be trained in the questionnaires and measurements prior to collecting any data. Completed data forms will be stored in a secure locked central location. All data will be double entered, compared, and sealed in a password-protected electronic database before the randomization code is broken. All data discrepancies will be resolved by examination of the original data cards and discussion with the relevant field workers. The data set will be locked after all discrepancies have been resolved.

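### The only scheduled aggregate safety review includes trial staff, does not list deaths or fetal losses among its inputs, and is not complemented by any planned independent review by arm

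*Protocol article*

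**What the plan says.** All of this is in the protocol article.

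- **Data monitoring, the meeting.** The article says that "a data safety monitoring meeting will be held every other month". On who calls it: "The meeting will be convened by the Director of Nutrition for the Ministry of Health and Sanitation". On who attends: "Present at this meeting will be the director, a study nurse, the district health officer, and one of the investigators". On what is examined: "At the meeting routine morbidity data, enrollment data, and participant satisfaction will be reviewed". The minutes go to the national ethics committee.
- **Data monitoring, single events.** Adverse events are defined as reactions to the study food, vomiting, diarrhoea and allergic-type rashes. Each serious event leads to a special inquiry. Unexpected events go to the Director of Nutrition within 24 hours, and "a summary of the event will be given to the data safety monitoring board within 24 h of being informed". The principal investigator then reviews the event. An independent physician is consulted only if that information supports a possible link to the study. The conclusions go to both ethics bodies. The board appears only here; neither its members nor its relation to the meeting is given.
- **Randomization and blinding.** The trial is open: "neither the study subjects nor the research study team members working directly with participants will be blinded". The masking offered is this: "Study managers will be blinded to treatment during data analysis".
- **Data management and analysis.** Mortality is named as a data type alongside morbidity. On the order of steps: "All data will be double entered, compared, and sealed in a password-protected electronic database before the randomization code is broken".
- **Outcome measures.** Infant survival at 3 and 6 months is a secondary outcome.
- **Discussion.** The authors expect that providing the full standard of care may give the control group better outcomes than existing data would predict.

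**The concern.** The arms differ in food, azithromycin, testing and treatment for bacterial vaginosis, and the sulfadoxine-pyrimethamine schedule (Interventions to reduce inflammation). The package is meant to lower stillbirth, growth restriction and prematurity. If it raised the risk of any fatal outcome instead, single cases would seldom reveal it. Where perinatal loss is common, one stillbirth or one infant death rarely looks related to the study. Such a harm shows in cumulative counts set against the other arm, and the article plans no such comparison during the trial by people independent of it.

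At stake is how long a harmful difference could run unrecognised in a trial of 1514 women that expects 24 months of follow-up (Trial status). The point concerns participant safety and the credibility of oversight. It does not affect the validity of the birth-length analysis.

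**Working it through.** The plan states no figure on this point, so the main check sets its sections side by side. Two small calculations then show what a count without a split by arm can and cannot reveal.

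**1. Membership.** There are four attendees. The study nurse and the investigator belong to the trial. The Director of Nutrition and the district health officer are not described as trial staff. No statistician is listed.

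**2. Inputs.** Routine morbidity, enrolment and satisfaction are listed. Maternal deaths, fetal losses, infant deaths, serious events and losses to follow-up are not. Data management and analysis names mortality separately from morbidity, so routine morbidity cannot safely be read as including deaths.

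**3. Comparison by arm.** None is mentioned under Data monitoring, Data management and analysis, or Statistical analysis. Whether the morbidity figures at the meeting are split by arm is not said.

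**4. Single-event route.** The order is inquiry, notice to the Director, summary to the board, principal investigator's review and then, conditionally, an independent physician for that one case. No step adds up events or compares arms.

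**5. Stillbirth or infant death, with assumed rates.** The article gives no such rates for this population, so a range is shown. Each arm has 1514 / 2 = 757 women, about 378 at half enrolment. Expected deaths are 378 × rate. Power is for a two-sided 0.05 comparison of two proportions.

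| Assumed rates | Deaths at 378 per arm | Total | Common rate giving the same total | Power by arm at 378 | Power by arm at 757 |
|---|---|---|---|---|---|
| 3% v 6% | 11.3 v 22.7 | 34.0 | 4.5% | 51% | 80% |
| 5% v 8% | 18.9 v 30.2 | 49.1 | 6.5% | 39% | 66% |
| 5% v 10% | 18.9 v 37.8 | 56.7 | 7.5% | 74% | 96% |

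In each row the total is what a single common rate would give (for example 756 × 0.065 = 49.1). Without a trusted background rate, the total cannot tell harm in one arm from a higher risk in both.

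**6. Maternal death, at the article's national rate.** The Abstract gives 1320 per 100,000 live births: 1514 × 0.0132 = 20.0 deaths. The Background section gives 1360: 1514 × 0.0136 = 20.6. If the risk doubled in one arm, the total would be 10 + 20 = 30.

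- If the background of 20 were known exactly, 30 or more would be unusual: Poisson probability about 0.02.
- The split 20/757 v 10/757 gives a two-sided Fisher p of about 0.10. Halfway, 10/378 v 5/378 gives about 0.30.

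For maternal death, then, the split by arm is itself weak evidence, and a total could be informative if the background were known. The national rate is a poor stand-in for it. It is counted per live birth, women with known complications are excluded (Eligibility criteria), and the Discussion expects better-than-usual outcomes in the control group. This calculation is an illustration and carries no weight in the conclusion.

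**The case against.** The strongest case on the other side has five parts.

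- **A reader might infer that the code is sealed, so no independent body can see a difference between arms.** The article does not support this. The sentence on sealing puts steps in order before the analysis. Participants and field staff know the allocation, so events could be tabulated by arm at any time. What is missing is a plan to do so.
- **A reader might infer that the meeting sees pooled figures only.** The text says routine morbidity and is silent on any split. Nor is it certain that a split by arm would breach the stated masking. That masking covers study managers during analysis, and the attending investigator is not said to be one of them. It would still show interim comparative results to an investigator.
- **A reader might infer that the board is just the meeting under another name.** Its membership is not given, which does not show that it has no members of its own. A charter may stand in the full protocol, and its absence from an article is no fault.
- **Oversight is not empty.** Two attendees come from outside the trial, every serious event triggers an inquiry, and both ethics bodies receive findings. It would be wrong to say that deaths come to light only after the last follow-up.
- **A table by arm has limited power**, as shown above.

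All five limit the claim. What remains is what the article does state: who attends, which inputs are reviewed, and a case-by-case route that passes through the principal investigator. The reports said to leave the trial are minutes and single-case findings, not counts by arm. Low power is a reason to read a table cautiously; it does not justify planning none.

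**Conclusion.** The point holds in a limited form. As described, the one recurring aggregate safety review includes two members of the trial team, and its listed inputs cannot show an excess of deaths in one arm. No section schedules a review by arm by people independent of the team, and the data safety monitoring board is not reconciled with the meeting. An excess of stillbirth, infant death or maternal death in one arm could go unnoticed while the trial runs.

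The size cannot be fixed from the article, which gives no stillbirth or infant death rates. Under the assumed rates, a difference of 3 to 5 percentage points is hidden in the total. A split by arm would give about 39% to 74% power at half enrolment and 66% to 96% with all women.

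The conclusion assumes that the stated attendance and inputs are complete, and that existing rates are a poor benchmark for the control group, as the Discussion indicates. A full-protocol charter that provides independent review by arm would reduce the point to a request to align the article with it. The change should be made; the primary analysis is not in question.

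**What to change.** 1. **Inputs (Data monitoring).** Add maternal deaths, fetal losses, infant deaths, serious events and losses to follow-up.
2. **Closed part of the same meeting.** Show these cumulatively by coded arm (A/B), with the number of women at risk in each. Only members outside the trial team attend: the Director of Nutrition and the district health officer, or the board already named. The study nurse and the investigator attend only the open part.
3. **Preparation.** The holder of the randomization list prepares the table.
4. **Data management and analysis.** State that this coded use of the allocation before data lock is allowed and does not count as breaking the code for the analysis.
5. **The board.** State who sits on it, what it sees, and whether it is the two-monthly meeting or a separate body.

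The cost is a small amendment to two sections and one short table every two months, or about 24 / 2 = 12 tables over the stated 24 months, fewer from now on because enrolment has begun. No new meetings or data collection are needed. The list holder takes on the work. Repeated looks at small counts will show chance imbalances, so the members should read the table as a safety signal and not as a test.
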